# Combined N-of-1 trials to investigate mexiletine in non-dystrophic myotonia using a Bayesian approach; study rationale and protocol

**DOI:** 10.1186/s12883-015-0294-4

**Published:** 2015-03-25

**Keywords:** Combined N-of-1 trials, Bayesian, Non-dystrophic myotonia, Mexiletine, Rare diseases, Skeletal muscle channelopathies

## Abstract

**Background:**

To obtain evidence for the clinical and cost-effectiveness of treatments for patients with rare diseases is a challenge. Non-dystrophic myotonia (NDM) is a group of inherited, rare muscle diseases characterized by muscle stiffness. The reimbursement of mexiletine, the expert opinion drug for NDM, has been discontinued in some countries due to a lack of independent randomized controlled trials (RCTs). It remains unclear however, which concessions can be accepted towards the level 1 evidence needed for coverage decisions, in rare diseases. Considering the large number of rare diseases with a lack of treatment evidence, more experience with innovative trial designs is needed. Both NDM and mexiletine are well suited for an N-of-1 trial design. A Bayesian approach allows for the combination of N-of-1 trials, which enables the assessment of outcomes on the patient and group level simultaneously.

**Methods/Design:**

We will combine 30 individual, double-blind, randomized, placebo-controlled N-of-1 trials of mexiletine (600 mg daily) vs. placebo in genetically confirmed NDM patients using hierarchical Bayesian modeling. Our results will be compared and combined with the main results of an international cross-over RCT (mexiletine vs. placebo in NDM) published in 2012 that will be used as an informative prior. Similar criteria of eligibility, treatment regimen, end-points and measurement instruments are employed as used in the international cross-over RCT.

**Discussion:**

The treatment of patients with NDM with mexiletine offers a unique opportunity to compare outcomes and efficiency of novel N-of-1 trial-based designs and conventional approaches in producing evidence of clinical and cost-effectiveness of treatments for patients with rare diseases.

**Trial registration:**

ClinicalTrials.gov Identifier: NCT02045667

## Background

Rare diseases constitute a heterogeneous group of over 6.000 disorders with a prevalence of <1 per 20.000. In Europe, 30 million patients (6 to 8% of the population) have a rare disease [1]. International regulatory authorities such as the Food and Drug Administration (FDA) and European Medical Agency (EMA) accept that it is unreasonable to demand the standard level of evidence (level 1) of multiple Randomized Controlled Trials (RCTs) in building an evidence-base for treatment of rare diseases [2-4]. The ability to conduct RCTs in rare diseases is hampered by low numbers of patients and large clinical heterogeneity. Relying simply on case reports or case series incurs a considerable risk of selection and ascertainment bias. Currently, it is unclear which concessions can be accepted towards the level 1 evidence needed for coverage decisions in case of rare diseases [5-7].

### The case of mexiletine treatment in Non-dystrophic myotonia (NDM)

NDM is a heterogeneous group of monogenetic rare diseases caused by mutations in the skeletal muscle chloride (*CLCN1*) or the sodium ion channel (*SCN4A*) genes. The key symptom is myotonia, a delayed relaxation after voluntary contraction resulting in muscle stiffness [8]. Apart from muscle stiffness, NDM patients also experience functionally limiting complaints of pain, fatigue and weakness [9].

For years, mexiletine (a sodium channel blocker) was considered the drug of choice for NDMs based on clinical experience. The immediate occasion for our study was the decision by the National Health Insurance Board of The Netherlands (and of some other countries), in 2006, to discontinue reimbursement of mexiletine as rational pharmacotherapy for patients with NDM [10,11]. This decision was based on a Cochrane review that reported the absence of two independent level-1 evidence studies showing an effect of mexiletine for NDM [12]. Additionally, because of the lack of precise prevalence numbers of NDM in The Netherlands, the rarity of the disease was taken into question. As a result, many of these patients had to discontinue their mexiletine treatment that seemed clinically effective.

In 2012, the Consortium of Clinical Investigation of Neurological Channelopathies (CINCH) performed an international multicenter cross-over RCT that showed the clinical effectiveness of mexiletine as treatment for patients with NDM over 4 weeks of therapy [13]. Although a prospective RCT is the gold standard, the effort involved in conducting such a trial (as well as time, funding and international cooperation) was substantial, and it will not always be feasible for rare diseases. New innovative trial designs may be used to ameliorate problems with small patient numbers and large clinical heterogeneity.

### Combined N-of-1 trials using a Bayesian approach

In an N-of-1 trial, multiple pairs of active treatment and placebo are offered to an individual patient in a randomized, double-blind fashion, while regularly measuring key endpoints, until efficacy is established or disproved [7].

Due to their design, in which each treatment-pair should be exchangeable in time, N-of-1 trials are especially suitable for the investigation of treatments in chronic, symptomatic conditions, where period effects (i.e. changes in disease state) and carry over effects (i.e. lingering drug effect) are small. This is the case for a number of neurological, reumatological, psychiatric and pulmonary disorders [14]. N-of-1 trials are hardly applicable to surgical, quickly progressive or acute medical conditions [15]. The method has been originally developed to identify the best treatment option for an individual patient in case of genuine doubt concerning treatment benefit by formalization of what a physician does on a daily basis [14,16].

Major advantages of N-of-1 trials from the point of view of the patient and the treating physician are: (1) an N-of-1 trial determines whether the treatment is actually of benefit in the individual patient as opposed to some percentage of a group of patients; (2) the N-of-1 trial avoids the possibly unethical “therapeutic misconception” of the RCT - where most subjects are convinced they are receiving effective treatment even though told there is a 50/50 chance they will receive placebo (and that the treatment may not be effective) [16-19].

More recently, data from multiple N-of-1 trials have been combined (or meta-analyzed) to produce estimates of treatment effect at a population level (i.e. combined N-of-1 trials) [20-22]. For this purpose, Bayesian hierarchical models have been developed [23,24]. Bayesian models use a different approach, which does not rely on the hypothesis testing/confidence intervals paradigm of traditional (frequentist) statistical methods, but allows determination of the posterior probability of whether a treatment effect is beneficial. Additionally, Bayesian methods allow for the use of prior available information (e.g. previous trial results) within the analysis [7].

### Hypothesis

The key hypothesis is that combining data from multiple N-of-1 trials using Bayesian statistics is a promising approach to produce evidence of clinical and cost-effectiveness of treatments for patients with rare diseases. As a case study we will investigate mexiletine in NDM. Results of this approach will be compared with the results of a conventional RCT approach.

Study objectives:(I).To use Bayesian methods for combining N-of-1 trials to obtain evidence of the clinical and cost-effectiveness of mexiletine in the treatment of NDM, on patient and population level simultaneously.(II).To compare this approach with a conventional RCT approach.

Both NDM and mexiletine are well suited for an N-of-1 trial design: NDM is a stable disease; mexiletine acts rapidly and its effect quickly subsides upon discontinuation of treatment; effects can be readily and objectively measured; and patients are eager to cooperate.

The Bayesian approach taken in this study will allow for considering questions on patient level and a population level simultaneously and it offers additional flexibility for customizing the trial length for individual patients. Furthermore, there is relevant clinical prior information (data from the previously conducted RCT) that can be incorporated into Bayesian analysis together with our new trial data.

## Methods/Design

### Design

In this study a series of double-blind, randomized and placebo-controlled N-of-1- trials is conducted. Each individual N-of-1 trial consists of one to four treatment sets, each comprising 11 weeks. A treatment set comprises two treatment periods: a four-week period of active treatment (mexiletine) and a four-week period of treatment with placebo, with a one-week wash-out in between treatment periods and two weeks for statistical analysis (individual interim analysis) at the end of each treatment set. Within each treatment set, the order in which mexiletine and placebo will be offered will be randomized (block-randomization). Total study duration will be between 11 and 44 weeks per patient, depending on the amount of treatment sets needed to produce convincing evidence of clinical effectiveness or ineffectiveness of mexiletine (Figure 1). Results of the individual N-of-1 trials will be combined to produce estimates of population clinical and cost-effectiveness by using a hierarchical Bayesian model [25]. The trial is performed at the Radboud University Medical Center in Nijmegen, The Netherlands.

**Figure 1 Fig1:**
[figure not shown]
**Study design individual N-of-1 trials.**

### Study population

Based on a sample size calculation (see below), thirty NDM patients will be included. Eligible patients have a genetically confirmed diagnosis of NDM, carry one (or two, in case of autosomal recessive inheritance) causative mutation(s) in the skeletal muscle chloride (*CLCN1*) or sodium (*SCN4A*) channel gene, and are at least 18 years of age and live in The Netherlands, Belgium or Germany.

A previous study in the Dutch NDM population showed a diagnostic yield of 100% for in tandem analysis of these two genes [26]. Inclusion and exclusion criteria, including co-medication are presented in Table 1.

### Recruitment and screening

Our center of expertise has developed a nation-wide registry of patients with NDM. As described previously, for this registry we asked all Dutch neurologists and the Dutch Patient Association for Neuromuscular Diseases (Spierziekten Nederland), to notify us of patients with NDM. Patients (>18 years) were invited to our neurology outpatient clinic in Nijmegen, The Netherlands, for clinical assessment, needle-EMG, and collection of blood samples for genetic analysis [8,12,26-29]. In 2007, the registry contained 62 NDM patients with a genetically confirmed NMD. Between 2007 and 2014, 48 genetically confirmed patients have been added, resulting in a total of 110 registered patients with extensive phenotypic and genotypic characterization. Asymptomatic carriers are not represented in the registry.

Potentially eligible patients will be selected from the registry. We expect that a maximum of 40% may not be eligible to participate, because of cardiac conditions, kidney or hepatic failure or neurological diseases other than NDM. Out of the remaining patients, random stratified samples will be taken, of 15 patients with a chloride channelopathy (TMC or BMC) and 15 patients with a sodium channelopathy (PMC or SCM). During a screening visit information about the study will be given, and patients will be asked to provide written informed consent. Eligibility will be checked by taking medical history and by conducting venous blood test (blood urea nitrogen, serum chloride, carbon dioxide, creatinine, blood glucose, serum potassium, serum sodium), ECG, and urine pregnancy testing for females. Serum pregnancy testing can be performed if, in the opinion of the investigator, the urine pregnancy test is inconclusive. Dosage, duration and date of last use of phenytoin, carbamazepine or mexiletine will be documented.

We will document characteristics of ineligible or excluded patients to estimate the external validity of our findings. Participants who are taking antiarrhythmics or medication that may affect sodium channels, will have a wash-out period before the baseline visit (Table 1, point 7). For the duration of the study, patients are instructed to comply with the study medication regime as supplied in the treatment kits.

### Intervention

Treatment conditions:Mexiletine hydrochloride 200 mg capsules, three times daily per os (PO)Placebo capsules, three times daily PO

### Randomisation and preparation of study drugs

A statistician will generate computer-based randomization schemes, and will send these to the hospital pharmacy that is in charge of the distribution of medication. Mexiletine will be purchased from Agenzia Industrie Difesa - Stabilimento Chemico Farmaceutico Militare in Florence (Italy) where mexiletine is produced under Good Medicinal Practice (GMP) conditions. Mexiletine will be released by a Qualified Person.

Treatment kits will be prepared by the department of Pharmacy of our hospital. Following computer-generated randomization drug packaging and labelling will take place at our department of Pharmacy. At the start of the first set (see below) patients will receive a blinded, randomly-ordered treatment kit that contains medication for the entire set. In each set, patients will receive 4-week treatment with mexiletine, 200 mg 1 times a day PO (first week, day 1), 200 mg 2 times a day PO (first week, day 2) and 200 mg 3 times a day PO (remaining days of first week and second, third and fourth week), placebo will be provided in a similar build-up scheme with placebo tablets PO. The placebo is microcrystalline cellulose (supplied by Spruyt Hillen). The mexiletine and placebo are standard orange colored capsules (size nr. 00). We will count capsules to determine compliance at the end of the study. In case of study discontinuation, reasons will be documented.

### Outcomes and measurements

#### Primary outcome measure

##### Interactive voice response diary (IVR)

The primary endpoint will be the severity score of stiffness reported via the IVR. The primary endpoint is the same as in the RCT by Statland et al. [13]. The IVR is an automated centralized, real-time response phone-system that records severity and frequency of symptoms (stiffness, pain, weakness, and tiredness) and has been validated in patients with myotonia [30]. Patients will call in on a daily basis during the last two weeks of each four-weeks treatment period to rate (1) if they experienced symptoms during the past 24 hours and (2) the severity of the symptoms on an ordinal scale (1 to 9; 1 being minimal and 9 the worst ever experienced) using their telephone key pad. The IVR has been translated for this study [30].

#### Secondary outcome measures

Severity scores of pain, weakness, and tiredness will be documented as measured by the IVR from daily calls made by participants during the last two weeks of each four-weeks treatment period.

##### Questionnaires

The Individual Neuromuscular Quality of Life questionnaire (INQoL) has been validated in skeletal muscle channelopathies such as NDM [31]. The questionnaire consists of 45 questions within 10 sections, four sections focus on the impact of muscle disease symptoms, five sections focus on the impact of muscle disease on particular areas of life, and one section focuses on the positive and negative effects of treatment. A composite score can be derived representing overall QOL. No Dutch version was available. With granted authorization from the authors, a translation into Dutch language has been used in patients with a chronic neuromuscular disease [32].The Short-Form 36-Item Health Status Survey (SF-36, Dutch version) is a generic questionnaire to establish the self-reported health status of patients. The questionnaire consists of the following domains: physical functioning (10 items), role functioning physical (four items), social functioning (two items), body pain (two items), mental health (five items), vitality (four items), general-health perception (five items), and change in health [33]. In addition summary composite scores for mental and physical functioning are derived. SF-36 domain scores from a Dutch nationwide sample of healthy individuals have been published [34].

##### Standardized interview

All interviews will be conducted by the same investigator ([name]). During the screening visit, answers to four open, standardized questions will be noted and recorded on video: 1. What is the most invalidating symptom or daily life disability that would make you take anti-myotonic medication? 2. Do you expect mexiletine to have a positive effect on your myotonic symptoms? 3. What kind of improvement would you need to experience for you to continue mexiletine treatment after the trial? 4. How important is a positive treatment-effect for you?

Apart from the standardized interview, co-morbidity, previous and current use of medication (also anti-myotonic treatment) will be reported. After each treatment set, the patients’ preference for one of the two treatment periods within the treatment-set, will be noted.

##### Clinical myotonia bedside tests

Eyelid closure action myotonia is defined as an increased muscle relaxation time of the orbicularis oculi and smaller upper and lower eyelid muscles (often between 1 – 15 sec) after forceful eyelid closure. The participant will be instructed to close the eyes as forcefully as possible for five seconds then rapidly open their eyes on command. This will be repeated five times in sequence. For each attempt, the time from the command to open their eyes until relaxation of the eyelid closure muscles will be timed and noted up to two decimals.Hand-grip action myotonia is defined as an increased muscle relaxation time of the finger flexor muscles and some of the involved underarm flexor muscles (often between 1 – 15 sec) after a forceful handgrip. The participant will be instructed to forcefully close the fingers of the right hand in a fist (handgrip) for five seconds, while resting the back of the right hand on a table, and then, on command, rapidly open the fist on command. This will be repeated five times in sequence. For each attempt, the time from the command to open the right fist until relaxation of the handgrip muscles to the point that the fingertips of dig II-V reach the surface of the table will be timed and noted up to two decimals. Both eyelid-closure action myotonia and handgrip action myotonia have been previously used to redefine clinical phenotypes [8] or as therapeutic outcome measure [13].The Timed Up&Go (TUG) measures the time in which the participant rises from a chair, walks three meters, turns around, walks back and sits down again in a self-selected speed. The TUG has shown intra- and inter-reliability and has been validated in patients with non-dystrophic myotonia [35,36].Quantitative Grip Myotonia: Maximum Voluntary Isometric Contractions (MVICs) of the long finger flexors and the subsequent relaxation time (myotonia) will be measured using a technique developed at the University of Rochester [37]. To measure the extent of grip myotonia of resting forearm muscle, each participant will squeeze the grip handle with a maximum grip for three seconds then relax until the force returns to baseline. The relaxation time from 90% to 5% of maximal force following this initial MVIC will be used to calculate the degree of myotonia. Each participant will perform three sets of five MVICs. Each set will be separated by a 10-minute rest period. Additionally, for each MVIC, we will analyze the peak force (PF) and the decline (%) of this PF within the three seconds duration of the MVIC (as a measure for the phenomenon of transient paresis).

All clinical myotonia bedside tests will be conducted by the same examiner ([name]).

##### Measurement of myotonic discharges with needle-EMG

Concentric needle EMG will be performed in the left rectus femoris muscle at rest. This muscle was chosen based on our previous studies on NDM [8,38]. According to established criteria of Streib et al. [39] myotonic discharges will be defined and quantified during 10 insertions, each followed by 30 sec of visual and auditory identification of myotonic discharges. Myotonic discharges must be at least 500 milliseconds, with potential amplitudes ranging from 10 μV to 1 mV, waxing and waning in both amplitude and frequency. Grading of myotonic discharges: 0: No positive muscle activity or an occasional run of positive waves following needle movement (detection of myotonia in 0-2/10 insertions); 1+: Myotonia fulfilling the minimal requirements (detection of myotonic discharges in 3-5/10 insertions) 2+: myotonic discharges in more than one-half of needle insertions (detection of myotonic discharges in 6-9/10 insertions); 3+: myotonic discharges with each needle movement in all examined areas (detection of myotonic discharges in 10/10 insertions) [39]. The EMG signals will be amplified and filtered between 20 Hz and 3 kHz and stored using the liveplay feature of the Medelec Synergy EMG equipment (software version 10; Oxford Instruments Medical, UK) to facilitate future quantification of myotonic discharge characteristics [38]. All needle-EMG investigations will be performed by or under supervision of an experienced clinical neurophysiologist ([name]).

### Mexiletine-serum concentration

Serum samples for random drug levels determination will be obtained during the visits at the start and end of every treatment period. All serum samples will be analyzed at once, at the end of the trial, by our department of Pharmacology and Toxicology. Analysis will be based upon a previously published protocol using liquid chromatography [40].

### Cost-effectiveness

Health care consumption will be assessed by using a modified version of the Client Service Receipt Inventory (CSRI), which will be filled in by the patients at the end of each treatment period [41,42]. The CSRI measures direct neuromuscular disease-related health care costs (including costs of visits to other health care providers: GPs, specialist care, physical therapy, psychological therapy, social worker contacts), professional home care and hospitalization, as well as non-health care costs such as costs for paid and unpaid help. Additional prescribed and over the counter medication will also be recorded. For unit cost prices, standard rates will be adopted from the national guideline [43] or real cost prices (e.g., for medication) will be obtained through the website of the Dutch Health Care Insurance Boards (Zorginstituut Nederland, http://www.medicijnkosten.nl). The price year will be 2014 and the currency Euros. Costs per patient will be calculated by multiplying resource volumes by unit costs. Costs and effects (in terms of QoL) will be combined to assess cost-effectiveness. If mexiletine appears to be more effective and more expensive –or less effective and less expensive- than placebo, the cost-effectiveness will be expressed in terms of the incremental cost-effectiveness ratio (ICER). Nonparametric bootstrapping techniques will be used to produce confidence intervals around mean costs, mean effectiveness and (if necessary) the ICER.

### General structure of the study

Initial screening will be scheduled 2 weeks prior to the baseline visit. During study enrolment patients will have 4-16 outpatient clinic visits depending on number of treatment sets necessary to obtain enough evidence (Figure 1). Each visit will take approximately 1-1.5 hours and comprises two questionnaires, clinical myotonia bedside tests, ECG and venous blood collection for measurement of mexiletine blood serum levels. Needle-EMG investigations will be performed at the end of each treatment period (Table 2).

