**Table 2 Tab2:** **Schedule of study measurements during the screenings phase and the first treatment set**

		**Mexiletine or placebo** ***(period 1)***				**Wash-out and cross- over**	**Mexiletine or placebo** ***(period 2)***				**Interim analysis 1**	
**Actions**	**Screening**	**Week 1, day 1**	**Week 2, day 1**	**Week 3, day 1**	**Week 4, day 7**	**Week 5**	**Week 6, day 1**	**Week 7, day 1**	**Week 8, day 1**	**Week 9, day 7**	**Week 10**	**Week 11**
**Lab test**	X											
**Pregnancy test**	X											
**Consent**	X											
**Medical history**	X											
**ECG**	X				X					X		
**Needle EMG**					X					X		
**IVR**		X	X	X*	X*		X	X	X*	X*		
**INQoL/SF-36**		X			X		X			X		
**Clinical myotonia tests**		X			X		X			X		
**Quantative grip myotonia**		X			X		X			X		
**Mexiletine blood plasma levels**		X			X		X			X		
**Dispense drug/ placebo**		X										
**Collect medication bottles**					X					X		

Study measurements for a possible second, third and fourth treatment set are identical to the measurements in the first treatment set and are not represented in this table.

X* = daily collection of IVR data.

Patients who exhibit convincing evidence of a genuine positive effect will be offered to continue to use mexiletine (see section: statistical analysis – individual interim analyses). After completion of the individual N-of-1 trials, patients will be followed up for three months, to monitor clinical progression, drug compliance, adverse events and quality of life.

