### Safety

ECGs taken at the beginning and end of each treatment period will be screened for abnormalities (conduction times: PR, QRS and QTc-time; and the presence of cardiac arrhythmia by an experienced cardiologist). Cardiac arrhythmias will be classified as clinically relevant or irrelevant. Clinically relevant arrhythmia and conduction disorders will be presented to the Data and Safety Monitoring Board (DSMB).

During the study, patients are instructed to directly report serious adverse events, non-serious adverse events (such as gastro-intestinal discomfort or nausea) are reported during trial visits.

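### The CSRI limits health care contacts to neuromuscular-disease-related care, so contacts for mexiletine side effects may go uncosted; the form is also missing from the visit description and Table 2

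*Protocol article*

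**What the plan says.** The first objective under Hypothesis is to "obtain evidence of the clinical and cost-effectiveness of mexiletine in the treatment of NDM", so costs are part of the main aim.

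The Cost-effectiveness section names one instrument for health care consumption, a modified CSRI, "which will be filled in by the patients at the end of each treatment period". On scope it states: "The CSRI measures direct neuromuscular disease-related health care costs". The parenthesis that follows lists GP, specialist, physical therapy, psychological therapy and social worker contacts. The sentence then continues with "professional home care and hospitalization, as well as non-health care costs such as costs for paid and unpaid help". A separate sentence adds other medication, both prescribed and bought without prescription, with no stated link to the disease. Costs and quality-of-life effects are then combined and, where applicable, expressed as an ICER.

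Under Safety, "non-serious adverse events (such as gastro-intestinal discomfort or nausea) are reported during trial visits", and ECGs are screened for conduction abnormalities and arrhythmia. Nothing there or in the Cost-effectiveness section says whether care for such events is costed.

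On logistics, General structure of the study says "Each visit will take approximately 1-1.5 hours and comprises two questionnaires, clinical myotonia bedside tests, ECG and venous blood collection". Table 2 names INQoL and SF-36 in its only questionnaire row and has no CSRI or cost row. Its footnote says: "Study measurements for a possible second, third and fourth treatment set are identical to the measurements in the first treatment set".

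**The concern.** The main issue is scope. An incremental cost for a drug should include the care that the drug itself causes. The health care contacts on this form carry a disease qualifier, and the side effects that the protocol anticipates or monitors for are gastro-intestinal and cardiac. Patients complete the form themselves, so unless it says otherwise they decide whether a GP visit for nausea belongs on it. If they leave it off, the loss is not balanced between arms, because drug side effects arise mainly on mexiletine. The measured cost difference would then be too small and the ICER would lean towards mexiletine. That matters here because the Background gives a reimbursement decision as the occasion for the study.

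The smaller issue is that the section requiring the form and the two places describing visit content do not match.

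**Working it through.** **Scope, reasoned from the text.** The cost items fall into three groups:

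| Cost item | Disease qualifier? | Side-effect care captured? |
|---|---|---|
| GP, specialist and therapy contacts | Yes, stated | Not on a literal reading; the text does not settle it |
| Home care and hospitalization | Unclear whether the qualifier carries over | Unclear |
| Additional medication | None stated | Yes |

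Paid and unpaid help is counted separately, as a non-health care cost. The possible gap is therefore certain in location only for outpatient contacts, and possible for hospitalization and home care.

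**Direction.** Let p_M and p_P be the probabilities of a side-effect contact that is left off the form in a mexiletine and a placebo period, and c the cost of one contact. Then

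measured cost difference = true cost difference − (p_M − p_P) × c.

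If p_M exceeds p_P, as expected for drug side effects, the difference is understated. If the contacts are in fact recorded, both probabilities are zero and there is no bias.

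**Size, illustration only.** The protocol gives no contact rates or unit prices. Assume p_M − p_P between 0.10 and 0.30, and c between EUR 30 and EUR 150:

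- low: 0.10 × 30 = EUR 3 per four-week period
- high: 0.30 × 150 = EUR 45 per four-week period
- over 13 such periods: 3 × 13 = EUR 39 to 45 × 13 = EUR 585 per year

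The range is 15-fold (45 / 3). The yearly figures further assume that the same contact rate recurs every four weeks. The protocol offers no total or incremental cost to set them against.

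**Schedule, by count.** Table 2 has four visit columns per set at which clinic tests are done (Week 1 day 1, Week 4 day 7, Week 6 day 1, Week 9 day 7). Over 1 to 4 sets this gives 4 to 16 visits, which agrees with General structure of the study. The CSRI falls due twice per set:

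- per patient: 2 × 1 = 2 to 2 × 4 = 8 forms
- for 30 patients: 30 × 2 = 60 to 30 × 8 = 240 forms

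None of these has an entry in Table 2. The due dates do coincide with two existing visits, Week 4 day 7 and Week 9 day 7.

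**The case against.** The other side has good points, and most of them limit the concern.

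- *A reader might infer that side-effect costs are excluded.* No sentence says so. Care caused by the drug given for a neuromuscular disease could be called disease-related, and the wording of the modified form is not shown. This stands: the text is ambiguous and does not state an exclusion.
- *A reader might infer that the form counts nothing but neuromuscular care.* That is wrong. Other medication is recorded without restriction, so drugs taken for stomach complaints would be captured, and paid and unpaid help is counted too.
- *A reader might infer from Table 2 that the cost data will not be collected, or will be lost for good.* The documents do not support this. The Cost-effectiveness section fixes the timing, at visits that exist. Table 2 is visibly incomplete in other respects: treatment preference after each set and adverse event reporting have no row either. The phrase about questionnaires can be read as covering the two instruments described under that heading and used at every visit. A missed first-period form might also be completed at Week 6 day 1.
- *Disease-related costing is a legitimate choice.* With 30 patients and four-week periods, unrelated events can dominate all-cause costs. This is a real drawback of the wider scope, but a disease-related sub-total answers most of it.

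What remains is that the qualifier attaches to GP and specialist contacts, that the expected side effects are not neuromuscular, and that the text leaves the reader, and the patient filling in the form, to decide.

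**Conclusion.** The point holds in a limited form. As worded, the CSRI may miss GP, specialist and similar contacts for mexiletine side effects, and it is unclear whether the same limit reaches hospitalization and home care. Any omission would fall mainly on mexiletine periods and would understate its incremental cost. This conclusion rests on a literal reading of the disease qualifier and on side-effect contacts being more frequent on mexiletine than on placebo.

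The direction follows from those two assumptions. The size is not known: the euro figures are illustrative, and a material bias in the ICER has not been shown. The primary stiffness endpoint is unaffected.

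The absence of the CSRI from the visit description and Table 2 is a clerical inconsistency with a modest risk of missed forms.

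**What to change.** 1. In the Cost-effectiveness section and on the form, state that health care use for adverse events is recorded. One way is to record all health care use in the period whatever its cause, with disease-related costs reported as a sub-total. Say explicitly that hospitalization and home care follow the same rule.
2. Add a CSRI row to Table 2 at Week 4 day 7 and Week 9 day 7, which the footnote then carries to later sets. Adjust the questionnaire count in General structure of the study for those visits.

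The cost is one wording change on the form, one table row, a corrected phrase and a few more minutes at visits that already take place. The downside of the all-cause option is some added noise in total costs from unrelated care. Recording adverse-event contacts alongside disease-related ones, without going to all causes, would add less noise but would still ask patients to judge the cause.
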